##### Daytime Sleepiness

The Epworth Sleepiness Scale (ESS) is used to examine daytime sleepiness [43]. The ESS measures general level of daytime sleepiness and sleep propensity with 8 items. Each item is scored on a 4-point scale indicating the chance of dozing off, and the total score ranges from 0 to 24, where a higher score indicates more daytime sleepiness. A score of **≥**11 indicates clinically significant subjective sleepiness [43]. The ESS is widely used in TBI research [71] and has a reasonably high reliability [72].

##### Multidimensional Aspects of Fatigue

The Dutch Multi-Factor Fatigue Scale (DMFS) is used to measure the multidimensional aspects of fatigue. The DMFS is a newly developed questionnaire that examines several factors of fatigue following TBI, including impact of fatigue, mental fatigue, signs and direct consequences of fatigue, physical fatigue, and coping with fatigue [44]. The DMFS consists of 38 items rated on a 5-point Likert scale, with higher scores on each subscale indicating more severe fatigue. This questionnaire is specifically developed to measure the multiple facets of fatigue following acquired brain injury [44].

##### Subjective Sleep-Wake Patterns

The relevant questions of the consensus sleep diary, which is a standardized sleep diary developed by insomnia experts [45], are used to examine subjective sleep-wake patterns and for better interpretation of actigraphy data. The sleep diary includes the following core questions: (1) the time of getting into bed; (2) the time at which the individual attempted to fall asleep; (3) sleep-onset latency; (4) duration of awakenings; (5) time of final awakening; (6) final rise time; and (7) perceived sleep quality (rated via Likert scale) [45]. An additional question about napping/dozing is added. The diary is completed in the morning and is filled out for 7 consecutive days concurrent with the actigraphy. Sleep diaries are a reliable and validated measure to examine sleep [73].

##### Posttraumatic Stress Disorder

The presence of posttraumatic stress disorder (PTSD) is determined with the PTSD Checklist of the Diagnostic and Statistical Manual of Mental Disorders, fifth edition (DSM-5; PCL-5), a 20-item self-reported measure corresponding to the DSM-5 symptom criteria for PTSD [46]. Each item is rated on a 5-point scale Likert scale and the total score ranges from 0 to 80, where a higher score denotes more severe PTSD symptoms. A score of 33 or higher is suggested as the indication of PTSD [46]. The PCL-5 is a reliable measure with strong validity [74]. PTSD occurs in 18% to 27% of the cases following severe TBI [75,76]. To check whether PTSD is the underlying cause of elevated stress and as PTSD takes time to develop, the PCL-5 is only assessed at visits 2 and 4.

##### Coping Style

Passive reaction coping style and active problem-solving coping style are examined with the Utrechtse Coping Lijst (UCL), which will differentiate active approach versus passive approach [47]. As this study only includes active and passive coping, the questionnaire will consist of 14 items scored on a 4-point Likert scale. Scores for both subscales range from 7 to 28, where higher scores denote a higher preference for that coping style. Both subscales show fairly good internal consistency and reasonably high test-retest reliability in the Dutch population [77]. The UCL has been used in Dutch TBI patients before and showed limited variability over time, therefore, coping styles are only assessed at visits 1 and 4 [78].

##### Sleepiness Preceding the Task

Sleepiness before the PVT is assessed with the Karolinska sleepiness scale (KSS) [48]. The KSS consist of 1 item on a 9-point Likert scale ranging from extremely alert to very sleepy, great effort to keep awake, where a higher score denotes greater sleepiness. The subject indicates the sleepiness level of the preceding 5 min. The test-retest reliability and the construct validity of the KSS are high [79].

#### Statistical Analyses

Descriptive statistics will be used to present mean scores and SDs at each time point of the outcome measures and predictive variables. Normality and assumptions will be checked. Next, 2 linear mixed regression analysis [80] will be performed to evaluate the associations between the predictive (independent) variables (pain, cognitive impairment, physical activity, emotional distress, cognitive complaints, social support, and participation) and the primary end point (subjective sleep quality and fatigue) across time. For each of the 2 primary end points, we will first determine whether these associations with predictors change across the 4 time points (ie, time by predictor interactions). In case of a significant interaction, simple interaction contrasts comparing consecutive time points will be used to determine whether the association between predictor and primary end point decreases or increases. Bonferroni correction will be used to adjust for multiple testing.

For the secondary objectives, the temporal relation between objective fatigue, objective sleep, and the predictive variables of the biopsychosocial model will be examined with the same linear mixed-effects regression analyses as used for the primary objectives.

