**Objective:**

The aim of this study is to examine the development of fatigue and sleep problems following moderate to severe TBI and to explore the changes in underlying biological (pain, brain damage), psychological (emotional state), and social (support family, participation) factors across time.

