**Methods:**

This study is a longitudinal multicenter observational cohort study with 4 measurement points (3, 6, 12, and 18 months postinjury) including subjective questionnaires and cognitive tasks, preceded by 7 nights of actigraphy combined with a sleep diary. Recruitment of 137 moderate to severe TBI patients presenting at emergency and neurology departments or rehabilitation centers across the Netherlands is anticipated. The evolution of fatigue and sleep problems following TBI and their association with possible underlying biological (pain, brain damage), psychological (emotional state), and social (support family, participation) factors will be examined.

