The aim of the study is to examine the development of post-TBI fatigue and sleep problems longitudinally within a biopsychosocial model including several factors in moderate to severe TBI. The primary focus of the study will be on subjective fatigue and sleep problems post-TBI. We hypothesize that the associations between biopsychosocial factors and post-TBI fatigue and sleep problems change over time, that is, the associations with biological factors are strongest in the first 6 months and then decline, whereas the associations with psychological and social factors are initially weak but slowly increase and become apparent between 12 and 18 months. Previous research has shown a discrepancy between objective and subjective measures of fatigue and sleep in the TBI population [21,25]. Therefore, the secondary aim of the study is to examine the development of post-TBI fatigue and sleep problems with objective measures within a biopsychosocial model. In this paper, the design of the study will be presented.

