### Study Population

Moderate to severe TBI patients are being recruited from emergency, neurology, and rehabilitation departments in several hospitals and rehabilitation clinics across the Netherlands. On the basis of a linear mixed regression analysis with a medium effect size (*F*_*2*
_=0.15), 7 significant predictors, a statistical power of 0.8, alpha level of .05, and a high test-retest reliability of at least 0.8 of the main study variables, the required sample is 103 TBI patients [26]. A dropout of 25% during the 18-month follow-up is expected based on previous studies [27,28]. Therefore, 137 patients will be recruited to lead to a total of 103 TBI patients being available for the analyses.

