##### Social Support

The Multidimensional Scale of Perceived Social Support (MSPSS) is used to assess social support [40]. The MSPSS consists of 12-items examining perceived social support from family, friends, and significant other. Each item is rated on a 7-point Likert scale. The mean total score ranges from 1 to 7, where a higher score denotes more perceived social support. The MSPSS has shown good psychometric properties [40], and it has been used in TBI patients [65].

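### The development aim has no model-based estimate of mean fatigue or sleep over time, only raw visit means with 25% dropout expected

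*Protocol article*

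**What the plan says.** The Abstract (Objective) puts the course of the symptoms first: "The aim of this study is to examine the development of fatigue and sleep problems following moderate to severe TBI". Exploring the underlying factors follows as a second part. The Abstract (Methods) again names two targets: "The evolution of fatigue and sleep problems following TBI and their association with possible underlying biological" and other factors. The Introduction is narrower. It states "The aim of the study is to examine the development of post-TBI fatigue and sleep problems longitudinally within a biopsychosocial model", and its only hypothesis is about associations: "We hypothesize that the associations between biopsychosocial factors and post-TBI fatigue and sleep problems change over time".

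The Statistical Analyses section gives each analysis a purpose. Level by visit is descriptive: "Descriptive statistics will be used to present mean scores and SDs at each time point of the outcome measures and predictive variables". One linear mixed model for each primary end point (FSS, PSQI) then relates the outcome to seven predictors. The terms tested are interactions of visit with predictor, followed by contrasts between neighbouring visits that show whether an association grows or shrinks. The objective outcomes get the same models.

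On retention, Study Population states: "A dropout of 25% during the 18-month follow-up is expected". It plans to recruit 137 so that 103 can be analysed.

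**The concern.** How tired patients are, how well they sleep at 3, 6, 12 and 18 months, and how much this changes are questions about means over time. No stated model, contrast or interval answers them. A reader of the results would have two substitutes, and each can mislead.

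- **Raw visit means** describe whoever attended. If leaving depends on earlier fatigue or sleep, the later means come from a selected group, and part of the apparent change is selection.
- **A time term from the predictor models** is change with pain, distress, participation and the rest held fixed. Table 1 shows all seven predictors measured at every visit, so they can change along with the outcome. Recovery that runs through mood or pain is taken out of such a term.

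The Introduction hopes to find periods in which targeted treatment is needed. A mis-stated course bears directly on that use.

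**Working it through.** **1. The plan's own figures.** Omnibus F test in multiple regression with f² = 0.15, 7 predictors, alpha .05, noncentrality 0.15 × N, df 7 and N − 8: the smallest N with power of at least 0.80 is 103 (power 0.8004). Dropout: 103 / 0.75 = 137.3, and 137 × 0.75 = 102.75, so 137 is consistent to within rounding. These figures are not in dispute. They size a test of the predictors, not a change in mean level. They also imply that about 34 of 137 patients (137 × 0.25 = 34.25) are lost by 18 months.

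**2. Targets against analyses.**

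| Target | Where named | Stated analysis |
|---|---|---|
| Course of fatigue and sleep | Abstract, Objective and Methods | Visit means and SDs, descriptive |
| Association with predictors | Abstract; Introduction | Mixed models |
| Change of association over time | Introduction (hypothesis) | Interactions and neighbouring-visit contrasts |

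The first row has no model-based estimate.

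**3. How far raw means could be off.** Only the 25% dropout comes from the protocol. Assumed: FSS SD 1.5, equal correlation between visits, nobody missing at 3 months, no return after dropout, and log-odds of leaving that rise with the previous score.

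*Check A: no true change, correlation 0.7, dropout 23% to 25%.* For log-odds of 0.5 to 1.5 per SD, the 18-month raw mean is off by −0.137, −0.246 and −0.294. A visit-only random-intercept model gives changes of 0.014, 0.024 and 0.012, against a truth of 0.

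*Check B: true change −0.30, dropout 25%, 200,000 simulated patients.* Raw change from 3 to 18 months:

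| Correlation | Log-odds 0 | Log-odds 0.5 | Log-odds 1.0 |
|---|---|---|---|
| 0.5 | −0.304 | −0.405 | −0.486 |
| 0.6 | −0.300 | −0.420 | −0.514 |
| 0.8 | −0.295 | −0.459 | −0.587 |

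Error = raw change − (−0.30). This is about 0 when dropout is unrelated to outcome, 0.105 to 0.159 in size at log-odds 0.5, and 0.186 to 0.287 at 1.0. Maximum likelihood with visit as the only factor gives −0.295 to −0.307 in all nine cells.

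Together the non-zero errors run from 0.105 to 0.294 FSS points, or 0.07 to 0.20 SD (0.105 / 1.5 and 0.294 / 1.5). For scale, the standard error of one visit mean with 103 patients is 1.5 / √103 = 0.15.

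**4. Why a conditional time term is not the trajectory.** Suppose a predictor falls by d SD between 3 and 18 months, has slope b (outcome SD per predictor SD), and accounts for all the change. The outcome then falls by d × b, while the time coefficient at fixed predictor is 0. With assumed d of 0.2 to 0.5 and b of 0.3 to 0.7, the fall that goes unseen is 0.2 × 0.3 = 0.06 to 0.5 × 0.7 = 0.35 SD.

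**The case against.** The strongest reply is that the analysis fits the aim as the Introduction words it. There, development is studied inside a biopsychosocial model, the only hypothesis concerns changing associations, and the planned interactions test it directly. A condensed article may also leave missing-data handling to a fuller document. Both points stand as far as they go: the hypothesis is served, and silence on missing data is not the fault raised here. Neither removes the separate target in the Abstract. The article does assign a purpose to each analysis, and none is given to the mean course beyond description.

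Four stronger readings are tempting, and the protocol does not support them.

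- *The aim rests on a time effect adjusted for all predictors.* Statistical Analyses never mentions a main effect of time or proposes to interpret one. Joint entry of the predictors is itself inferred, from there being two models and a seven-predictor sample size.
- *Nothing planned can estimate the trajectory.* Raw means do so without bias if dropout is unrelated to outcome. The predictor model could also yield marginal visit means if averaged over the predictor distribution at each visit, although no such averaging is stated.
- *Raw means will show false recovery.* The direction is assumed. If recovered patients leave instead, the error reverses. Home visits, allowed under Procedure, may weaken the link between fatigue and leaving.
- *Uncentred predictors spoil the models because the social support scale cannot be zero.* The scale does exclude zero ("The mean total score ranges from 1 to 7"), but no coding is stated. Centring on a constant leaves the planned interaction tests and contrasts unchanged.

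The simulations also favour the remedy by construction, because dropout depends on an observed score. If it depended on the unseen current score, the likelihood model would be biased too.

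**Conclusion.** The point holds in limited form. The protocol names the course of fatigue and sleep as a target in its own right but states no model-based estimate or contrast of their means over time. With 25% dropout, the raw visit means could mis-state the 3-to-18-month change by about 0.1 to 0.3 FSS points. That range rests on an assumed SD of 1.5, assumed correlations of 0.5 to 0.8, and an assumed dependence of dropout on the previous score. With no such dependence the error is zero, so the figures show what is possible and do not predict it. The planned tests of changing associations are unaffected. This should be changed because the better method is available on data already being collected, and it also supplies intervals for change, which the descriptive table does not.

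**What to change.** Before the predictor models, fit for FSS, for PSQI and for each objective outcome parameter a likelihood-based mixed model with visit as the only fixed factor. Use every observed visit of every enrolled participant, not only those who complete 18 months. Report estimated means at 3, 6, 12 and 18 months and changes from 3 months, with 95% CIs, and name this as the answer to the development aim. Keep the raw means and SDs as description. State that time terms from the predictor models are conditional on the predictors and will not be read as the trajectory.

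Patients who leave before 3 months have no FSS or PSQI score, since Table 1 has neither outcome at screening, and no model of these data recovers them. Their number should be reported.

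The cost is one simple model per outcome parameter. FSS, PSQI, the vigilance task and the three actigraphy sleep parameters named under Secondary Outcome Measures make 1 + 1 + 1 + 3 = 6, and more if further parameters are analysed. No new data are needed.

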**Group characteristics and monitor the participants**							
	TBI characteristics	Injury severity such as structural imaging data, LOC^c^, PTA^d^, injury severity score; causes of injury; comorbid (physical) injuries, seizures; drug or alcohol intoxication during injury from the hospital database.	✓	—	—	—	—
	Demographics	Age, gender, education, marital status, and work status	✓	—	—	—	—
	Premorbid sleep	Premorbid question of PSQI^e^ [33]	✓	—	—	—	—
	Premorbid participation	Premorbid frequency and satisfaction of the USER-P^f^ [39]	✓	—	—	—	—
	Daytime sleepiness	Epworth Sleepiness Scale [43]	—	✓	✓	✓	✓
	Multidimensional aspects of fatigue	Dutch Multi-Factor Fatigue Scale [44]	—	✓	✓	✓	✓
	Subjective sleep-wake	7 days sleep diary [45]	—	✓	✓	✓	✓
	Posttraumatic stress disorders	PTSD^g^ checklist for DSM-5 [46]	—	—	✓	—	✓
	Coping style	Proactive and passive coping scale of the Utrecht Coping List [47]	—	✓	—	—	✓
	Drugs/alcohol/medication use	Demographic questionnaire	✓	✓	✓	✓	✓
	Sleepiness preceding the task	Karolinska sleepiness scale [48]	—	✓	✓	✓	✓

^a^COWAT: controlled word association test.

^b^SDMT: symbol digit modalities test.

^c^LOC: loss of consciousness.

^d^PTA: posttraumatic amnesia.

^e^PSQI: Pittsburgh Sleep Quality Index.

^f^USER-P: Utrecht Scale for Evaluation and Rehabilitation-Participation.

^g^PTSD: posttraumatic stress disorder.

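### The stated mixed models hold only the seven biopsychosocial predictors and their time interactions; age, gender, education and premorbid sleep are collected but not adjusted for, leaving the predictor associations open to confounding

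*Protocol article*

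**What the plan says.** The Statistical Analyses section of the protocol article describes two linear mixed regressions, one for subjective fatigue and one for subjective sleep quality. The independent variables are "pain, cognitive impairment, physical activity, emotional distress, cognitive complaints, social support, and participation". The only further terms described are interactions of these predictors with time. For objective fatigue and objective sleep the section prescribes "the same linear mixed-effects regression analyses as used for the primary objectives".

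Two other places agree with that list. Table 1 has the same seven constructs under its predictor heading. The Study Population section sizes the study on "7 significant predictors, a statistical power of 0.8, alpha level of .05".

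Background variables have a different role. In Table 1, "Age, gender, education, marital status, and work status" and "Premorbid question of PSQI" are ticked at screening only, in the block for group characteristics and monitoring. No section says that any of them enters a model.

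**The concern.** The aim is explanatory. The Introduction and Discussion want to identify the factors that contribute to fatigue and sleep problems, and the Conclusions look to modifiable ones as a guide to interventions. In an observational design, such a reading needs control of obvious common causes.

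Cognitive performance is the most exposed predictor. The Cognition section uses the degree of impairment on the Stroop, COWAT, digit span and SDMT as a proxy for the severity of brain damage. Scores on tests of speed, interference and fluency plausibly differ by age and schooling in uninjured people as well. With entry open from 21 to 70 years, an unadjusted score mixes injury with age and education, and either may also relate to sleep or fatigue. Cognition also carries the brain-damage part of the hypothesis in the Introduction that biological associations are strongest in the first 6 months.

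For sleep, the premorbid PSQI item is the one pre-injury measure related to a primary endpoint, and no stated model uses it.

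**Working it through.** **1. Does the plan's own sample size match a seven-predictor model?**

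Inputs, all from Study Population: "On the basis of a linear mixed regression analysis with a medium effect size" (0.15, read as f²), 7 predictors, power 0.80, alpha 0.05. The method is the omnibus F test of a multiple regression, with noncentrality λ = f²·N, numerator df u = 7 and denominator df v = N − 7 − 1.

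- The smallest N with power of at least 0.80 is 103 (v = 95, λ = 0.15 × 103 = 15.45), with power 0.8004. The plan says "the required sample is 103 TBI patients", so the figure reproduces. The reliability assumption of 0.8 is not needed to obtain it.
- Dropout: 103 / 0.75 = 137.3. The plan recruits 137, and rounding up gives 138, an immaterial difference.

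The stated N therefore corresponds to seven tested predictors with no covariate degrees of freedom. This agrees with the model list but does not prove that covariates are excluded, as step 2 shows.

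**2. What would adjustment cost?**

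Keep the test on the seven predictors (u = 7, f² = 0.15) and add k covariate df, so v = N − 7 − k − 1.

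| Covariate df (k) | Required N | Power at N = 103 |
|---|---|---|
| 0 | 103 | 0.800 |
| 4 (age, gender, education, premorbid sleep) | 104 | 0.799 |
| 8 (for example, education in several categories) | 104 | 0.797 |

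This uses the plan's simple regression basis, not a full mixed-model power calculation.

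**3. How large might the confounding be?**

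The document gives no correlations, so these are assumptions. With age as the only link between cognition and outcome, the spurious correlation is r(age, cognition) × r(age, outcome).

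- Weak end: −0.3 × 0.1 = −0.03.
- Strong end: −0.5 × 0.3 = −0.15.

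For any predictor, omitting a covariate c shifts the standardised coefficient by about r(x,c) × β(c). With both between 0.1 and 0.3, the shift is 0.01 to 0.09. These are one-predictor illustrations; the other six predictors could reduce or increase the shift.

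**4. What happens to precision?**

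*Cognition coefficient when age is added* (same assumptions, no true link). The standard error is multiplied by √[(1 − r_ya²) / (1 − (r_xa·r_ya)²)] / √(1 − r_xa²).

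| r_xa | r_ya | Multiplier |
|---|---|---|
| −0.3 | 0.1 | 1.04 |
| −0.3 | 0.3 | 1.00 |
| −0.5 | 0.1 | 1.15 |
| −0.5 | 0.3 | 1.11 |

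The standard error is unchanged or up to about 15% larger.

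*Power for the seven predictors together* if the covariates explain additional outcome variance R²c (assumed). Hold the predictors' increment at 0.15 / 1.15 = 0.130, so that partial f² = 0.130 / (1 − 0.130 − R²c), with k = 4.

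| R²c | Partial f² | Power at N = 103 |
|---|---|---|
| 0 | 0.150 | 0.799 |
| 0.05 | 0.159 | 0.826 |
| 0.10 | 0.170 | 0.854 |
| 0.20 | 0.195 | 0.906 |

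A gain is possible, but it depends entirely on R²c.

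**The case against.** **A condensed article may simply not list its covariates.** The seven variables are those of scientific interest. The sentence also leaves out time as a main effect and the random-effects structure, and no section uses the word unadjusted. A fuller protocol or SAP, not shown, could add covariates or use age- and education-corrected test norms. This stands as a limit: the point concerns the model as written here. The list is nevertheless the same in three places, and a fourth gives the background variables another role, so this is more than silence.

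**The first test concerns change over time.** A confounder with a constant effect biases the overall associations more than the time-by-predictor interactions. This stands. A reader might infer that the central hypothesis test is invalid, and the document does not support that. The overall associations still matter, because the stated aim is to find contributing factors. A patient-level random effect would not remove between-patient confounding.

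**The variables are not wholly uncontrolled.** Entry criteria limit age and exclude pre-existing sleep-wake disturbance, fatigue from other medical conditions and previously treated mental disorder. This stands in part: restriction narrows the range, but variation remains.

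**Adjustment need not sharpen the estimates.** A reader might infer that standard errors are needlessly large throughout. Step 4 shows otherwise for cognition. Premorbid sleep, if correlated 0.3 to 0.5 with the PSQI (assumed, and perhaps optimistic after the exclusions), would cut only the between-patient standard error, by a factor of √(1 − r²) = 0.954 to 0.866.

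**The premorbid measures do not suit every model.** The sleep item is recalled after injury and is no baseline for fatigue. Premorbid participation would be tied to a single predictor, whereas the plan has one model per endpoint. Both points stand, and the fix respects them.

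**Conclusion.** The point holds for the model as stated: seven predictors and their time interactions, with no adjustment for age, gender, education or premorbid sleep. The exposure lies mainly in the overall predictor-outcome associations, above all for cognitive performance as the proxy for brain damage. It is smaller for the interactions, provided the confounder's effect is constant over time. The illustrative size is a spurious correlation of −0.03 to −0.15 for cognition, resting wholly on assumed age correlations.

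The case for adjustment is reduced confounding. Any precision gain depends on how much outcome variance the covariates explain, and cognition's standard error may widen. A reader might also infer that the sample size is wrong. It is not: 103 reproduces and barely moves. The requirement would rise to 123 (power 0.70 at 103) only if the four covariates were counted among the tested predictors in an 11-df omnibus test, which adjustment does not require.

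**What to change.** In the Statistical Analyses section:

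- State that age, gender and education enter all primary and secondary mixed models as fixed covariates (main effects).
- Add the premorbid PSQI item to the sleep models, the PSQI model first.
- Keep the tests on the seven predictors and their time interactions.
- Report the seven-predictor model without covariates as a sensitivity analysis.

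The cost is a change of wording and a few degrees of freedom. The data are already collected at screening, so no new measurement is needed. On the plan's own basis the required analysable number goes from 103 to 104, with power 0.799 at 103, so the recruitment target need not be reworked.

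### Single-step Bonferroni is valid, but Holm's step-down procedure gives the same familywise error control with at least as much power in whatever family the plan uses

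*Protocol article*

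**What the plan says.** In Statistical Analyses, one linear mixed model is planned for each primary end point (Fatigue Severity Scale and Pittsburgh Sleep Quality Index), with seven predictors: "pain, cognitive impairment, physical activity, emotional distress, cognitive complaints, social support, and participation". The first step is to determine "whether these associations with predictors change across the 4 time points (ie, time by predictor interactions"). The second step depends on the first: "In case of a significant interaction, simple interaction contrasts comparing consecutive time points will be used". With visits at 3, 6, 12 and 18 months there are three such contrasts per predictor and end point. The section then fixes the method of adjustment: "Bonferroni correction will be used to adjust for multiple testing". No step-down or closed procedure is named, and the article does not say which tests form the family. The secondary outcomes use the same analyses.

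The sample size in Study Population rests on "7 significant predictors, a statistical power of 0.8, alpha level of .05" and an effect size of 0.15.

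**The concern.** The primary hypothesis concerns when associations weaken or strengthen after injury, so it is carried by these interaction and contrast tests. Single-step Bonferroni compares every p-value in a family of m tests with alpha/m, even after some hypotheses in that family have been rejected. Holm relaxes the threshold after each rejection at no cost in familywise error. The plan also requires a significant interaction before it looks at the contrasts, yet plain Bonferroni draws no benefit from that requirement. What is at stake is avoidable loss of power in the main analysis. False-positive control is not threatened.

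**Working it through.** **The plan's own figure.** The required sample is 103. Take the noncentral F test of R² = 0 with 7 predictors, f² = 0.15, noncentrality 0.15 × N and alpha .05. Power is 0.7954 at N = 102 and 0.8004 at N = 103, so 103 reproduces. Dropout gives 103/0.75 = 137.3 (the article states 137). Neither figure depends on the multiplicity method. The reproduction shows that the seven predictors enter as the degrees of freedom of one overall regression test.

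**Holm against Bonferroni, any family of m tests.** Bonferroni compares every p-value with alpha/m. Holm compares the i-th smallest with alpha/(m − i + 1) and stops at the first failure. The first threshold is the same (alpha/m) and later ones are larger, so Holm rejects everything Bonferroni rejects. For m = 7 the Bonferroni threshold is .05/7 = .0071; Holm's thresholds run .0071, .0083, .0100, .0125, .0167, .025, .05. Holm's error control needs no assumption about dependence. The chance of at least one rejection is unchanged; the gain is in the second and later rejections.

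**Size of the gain for interactions.** Four visits give 3 df per interaction. The article gives no interaction effect sizes, so power per test is an assumption and a range is shown. A noncentrality of 10.90 gives 80% power at .05. Simulated average power over the real interactions, independent tests, 80% power each at .05:

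| Family | Real | Bonferroni | Holm |
|---|---|---|---|
| 7 | 3 | 55.1% | 57.6% |
| 7 | 5 | 55.1% | 60.9% |
| 7 | 7 | 55.1% | 66.6% |
| 14 | 14 | 46.4% | 56.1% |

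With 7 of 7 real, the gain is about 12 points at 80% power per test, 5 at 60%, 3 at 50% and 2 at 40%. With 3 of 7 real, it is about 2.4 points at 80% and 0.5 at 40%.

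**The contrasts of one predictor and one end point.** The 3-df interaction null is the same statement as all three consecutive differences being zero. Once it is rejected, at most two can be zero. Ordered thresholds alpha/2, alpha/2, alpha (Shaffer's logical restriction) are then enough, that is .025, .025, .05. Bonferroni uses .0167 throughout, and Holm .0167, .025, .05. Simulation (400,000 runs; four visit-specific slopes with equal SE; interaction gate at .05; true contrasts assumed at 2.80 SE, which is 80% power at .05, or 3.24 SE, which is 80% power at .0167):

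| True contrasts | Power for | Bonferroni | Holm | Gated step-down |
|---|---|---|---|---|
| one, 2.80 SE | that contrast | 64.4% | 64.6% | 68.6% |
| one, 3.24 SE | that contrast | 79.4% | 79.5% | 82.7% |
| two, 2.80 SE | both | 36.6% | 45.1% | 45.4% |
| two, 3.24 SE | both | 61.0% | 68.7% | 68.8% |
| three, 2.80 SE | all three | 18.8% | 43.8% | 43.9% |

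Familywise error within this family, in the same order:
- all null: 0.030, 0.030, 0.035
- one very large effect, two nulls: about 0.032, 0.047, 0.047
- two very large effects, one null: 0.017, 0.050, 0.050

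All are at or below .05 within simulation error.

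**Where the gated thresholds stop being valid.** They control error only inside one predictor and one end point.
- There are 7 × 2 = 14 interactions. If each is gated at an unadjusted .05 and all are null and independent, the chance of at least one false opening is 1 − 0.95^14 = 51%.
- Suppose every opened gate has one large true step and two null contrasts. The chance of at least one false contrast is 1 − (1 − 0.0467)^7 = 28% over 7 opened gates and 49% over 14. With .05/42 it is 1.6% and 3.2%.
- If the family is all 7 × 2 × 3 = 42 contrasts, Bonferroni's threshold is .05/42 = .00119, and Holm's first two are .00119 and .05/41 = .00122. Starting at .025 would be a different and much weaker standard.

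**The case against.** The strongest reply is that nothing here is wrong: a valid, conservative correction is prespecified, and a condensed article may leave the exact procedure and its families to an analysis plan. The first part stands, and the point is therefore put as an improvement. The second stands for the families, whose absence is not raised. It does not cover the method, which the article states outright.

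Three stronger readings are tempting, and the document does not support them.
- A reader might infer that alpha/2, alpha/2, alpha can replace Bonferroni for the contrasts whatever the family. That holds only within one predictor and one end point. If the authors' Bonferroni spans predictors or end points, the replacement would loosen error control.
- A reader might take "7 significant predictors" as the authors' assumption that seven interactions are real, which is where Holm gains most. The phrase is an input to a regression sample-size calculation and says nothing about interactions.
- A reader might take the 12-point gain as the expected one. It is the most favourable of the family-of-seven cases: independent tests, all real, each with 80% power. None of these conditions is in the article, and 103 was not derived for 3-df interaction tests.

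Bonferroni also has one real advantage: simultaneous intervals that agree with its tests. That is useful in an observational study of changing associations, although the article does not call for such intervals.

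**Conclusion.** The point holds as a near-costless improvement. In any fixed family, Holm matches Bonferroni's familywise error guarantee and never rejects less; this needs no assumption about effect sizes or dependence. The amount gained does depend on assumptions. For seven independent interactions, all real, it runs from about 2 to 12 points of average power as power per test goes from 40% to 80%, and it is smaller when few are real. Among three gated contrasts, Holm gains 0.1 to 0.2 points when one is real and about 8 points in the power to find both when two are. The gated start adds 3 to 4 points in the one-contrast case, only under the family restriction above. The protocol's type I error control is not in question, and the sample size figures are unaffected.

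**What to change.** Replace the Bonferroni sentence by: *Holm's step-down procedure will be used, within the same families, to adjust for multiple testing.*

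Optionally add: *Where the family is the three consecutive-visit contrasts of one predictor and one end point, opened by an interaction test that is significant after multiplicity adjustment, the ordered contrast p-values will be compared with alpha/2, alpha/2 and alpha.* If the family spans predictors or end points, leave this out and use plain Holm over that family.

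The cost is one or two sentences of analysis wording, with no change to data, visits or recruitment. The downside is that simultaneous confidence intervals no longer match the tests exactly. If unadjusted 95% intervals are shown beside Holm-adjusted p-values, label them as unadjusted, because some may exclude zero where the adjusted test does not reject.
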